**Neonatal outcomes**
Breastfeeding issues
Transient tachypnea of the newborn (TTN)
Respiratory distress syndrome (RDS)
Intracranial hemorrhage
Brachial plexus injury
Other neurologic injury
Neonatal sepsis
Neonatal jaundice
X-ray suggestive of alveolar disease
Admission in NICU
Admission for more than 48 h in NICU
Other

A separate questionnaire has been created to calculate professionals’ willingness to change: this will be completed by all participating obstetricians prior to the intervention period. The Head Obstetrician of each unit fills out another questionnaire, his perception being given special attention. Obstetric practice trends may also be affected by the perceptions and routine practice of other medical specialties in close collaboration with the obstetric unit. Thus, two different questionnaires will also be sent to the Head Anesthesiologist and the Head Neonatologist/Pediatrician of each participating hospital (unit).

The REDCap electronic data platform will be accessed by all participating professionals to insert their data. REDCap is a secure web-based application developed to capture online and offline data for clinical research and operations and to build and manage online surveys and databases. The platform is designed to provide a safe environment so that researchers may collect and store highly confidential and sensitive medical information, while access is limited to authorized persons. All participating women will be included in the data analysis.

This is an anonymous study and no personal identifiers will be transmitted. We will not retain any identity information about the participating women and their babies. The data contained in the current study will be kept strictly confidential, while all research records will be stored in a locked file and all electronic information will be coded and secured using a password-protected file. No personal information will be included in any report we may publish which would make possible identification of the obstetricians or women who participated. The participating obstetricians or any of the pregnant women that they care for will be aware that they can decline to take part in the study without affecting their care or the relationship of the pregnant woman to her obstetrician. They will moreover know that they are entitled not to reply to any question and to opt out at any time during the study period. The trial committees will be available to respond to any further queries about the study. Finally, the participating women will be able to access a summary of the study’s anonymous results uploaded on the trial’s webpage after the conclusion of the study. For the obstetricians, this information will be provided with particular details of their unit performance.

### Statistical analysis

All relevant baseline individual and hospital characteristics will be summarized both overall and by trial arm period. The main analysis of the primary outcome will be based on a generalized logistic regression mixed effects model, with covariates for the trial arm and a categorical term for any underlying trend. The primary effect measure will be the odds ratio for the arm estimated from this model. Depending on the data, to increase precision, the primary model may include parametric modeling of any secular trend rather than categorical.

Sensitivity analyses of the primary outcome (and primary model) may include extensions to allow for varying secular trends between clusters (random effect for time) and varying treatment effect across clusters (random interaction between cluster and trial arm). Effect modification by cluster strata (e.g., public/private) may be explored by the inclusion of a fixed effect interaction between cluster strata and arm.

Although not expected, if baseline imbalances are obvious and of clinical relevance between control and intervention periods, the above models may be adjusted for these imbalances via a further sensitivity analysis. Moreover, if any hospitals display non-adherence to the intervention guidelines, a per-protocol analysis may be conducted ensuring proper adjustment for relevant differences between those who adhere and those who do not.

Secondary outcomes of maternal and neonatal morbidity and mortality will be displayed descriptively and, where possible (sample size permitting), analyzed similarly to the primary outcome.

There will be no interim analyses as safety is not a concern. Significance of any difference in the primary outcome is set at 0.05 and at 0.01 for additional secondary outcomes. All analyses will be conducted using R statistical software.

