**Methods:**

Twenty-two selected maternity units in Greece will participate in a multicenter stepped-wedge randomized prospective trial involving 20,000 to 25,000 births, with two of them entering the intervention period of the study each month (stepped randomization). The maternity care units entering the study will apply the suggested interventions for a period of 8–18 months depending on the time they enter the intervention stage of the study. There will also be an initial phase of the study lasting from 8 to 18 months including observation and recording of the routine practice (cesarean section, vaginal birth, and maternal and perinatal morbidity and mortality) in the participating units. The second phase, the intervention period, will include such interventions as the application of the HSOG (the Hellenic Society of Obstetrics and Gynecology) Guidelines on labor management, training on the correct interpretation of cardiotocography, and dealing with emergencies in vaginal deliveries, while the steering committee members will be available to discuss and implement organizational and behavioral changes, answer questions, clarify relevant issues, and provide practical instructions to the participating healthcare professionals during regular visits or video conferences. Furthermore, during the study, the results will be available for the participating units in order for them to monitor their own performance while also receiving feedback regarding their rates. Τhe final 2-month phase of the study will be devoted to completing follow-up questionnaires with data concerning maternal and neonatal morbidities that occurred after the completion of the intervention period. The total duration of the study is estimated at 28 months. The primary outcome assessed will be the cesarean section rate change and the secondary outcomes will be maternal and neonatal morbidity and mortality.

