### Data

The ideal goal is to accumulate 20,000–25,000 deliveries, the sample size having been estimated based upon hospital birth rates for the year 2019. Based on these data, an assumed 57% cesarean rate (also from 2019 data) across centers, an intracluster correlation (ICC) of 0.3, a negligible secular trend, and a significance level of 0.05, we have > 99% power to detect an 8% absolute reduction in cesarean section rates (OR = 0.72). This calculation is based on the method of Hussey and Hughes, which assumes equal cluster sizes. Given that in this trial there is a large variation in the number of deliveries per hospital this assumption may be violated. To ensure the estimated power is robust to this and across possible randomization sequences, we carried out a simulation study. The parameters for the simulation were the same as those above, other than allowing for varying hospital sizes. The ICC was also varied to assess robustness to higher/lower values. In all scenarios, the available sample size resulted in >95% power. All simulations were conducted using R statistical software.

Intervention is the task of the obstetricians of the participating hospitals, but the analysis and conclusions will be derived from mothers and infants by calculating cesarean section rates and maternal and neonatal morbidity. While our intervention is aimed at introducing modifications and improvements within the national public and private health system, the evaluation will take place on both a local and a national basis.

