The main outcome of the study will be the change in the cesarean section rates and how effective the particular interventions are. The secondary outcomes of the study will be the maternal and neonatal morbidity that has occurred (Tables 6 and 7). The outcome variables will be the percentage of primary and secondary outcomes measured during the intervention period and the 2 months following the end of the intervention (rollout period). The amassed data will be employed in order to examine the potential for confounding of the intervention’s main effect on account of imbalances due to group randomization. There will be a clear separation of the data collection system for the determination of outcomes from the execution of the interventions. It will not be possible to blind the randomization due to the nature of the intervention; thus, data collectors will know whenever they are participating in the intervention. Finally, because the ability of participating hospitals to collect and review clinical data might possibly introduce bias into the outcome assessment, the data collection system will be, as far as possible, isolated from the intervention instruments to minimize the bias.

**Table 6 Tab6:** Maternal morbidity questionnaire: list of complications, diseases, and operations that will be included in the trial

**Maternal primary outcomes**	**Maternal secondary outcomes**
Manual removal of placenta	PPH (postpartum hemorrhage, secondary)
PPH (postpartum hemorrhage)	Removal of retained products (curettage, medicines)
Tachypnea /Bradypnea	Anemia
Oliguria that does not respond to fluids or diuretics	Blood transfusion
Inability to form clots (clotting disturbances)	Hysterectomy
Shock	Thrombosis/embolism
Cardiac arrest (absence of pulse and loss of consciousness)	Ileus
Cardiopulmonary resuscitation	Necrotizing enterocolitis
Severe acute thrombocytopenia (< 50,000 platelets/mL)	Fistulas
Red blood cell transfusions (≥ 5 units)	Wound dehiscence
ICU (intensive care unit) admission	Trauma infection
3^rd^ or 4^th^ degree perineal tear	Prolonged bladder catheterization
Uterine rupture	Urinary tract infection
Laparotomy (including hysterectomy)	Endometritis
Preeclampsia/eclampsia	Puerperal fever
Stroke	Sepsis
Uncontrolled convulsions/status epillepticus	Pelvic organ prolapse
Permanent neurological injury	Incontinence
Other	Puerperal psychiatric disorders

**Table 7 Tab7:** Neonatal morbidity, complications, and their monitoring

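### The outcome and planning target are absolute changes in cesarean rate, but the only effect measure named is a unit-specific odds ratio, which cannot be set against the planning odds ratio of 0.72

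*Protocol article*

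**What the plan says.** The Methods part of the Abstract states: "The primary outcome assessed will be the cesarean section rate change". The Data section agrees: "The main outcome of the study will be the change in the cesarean section rates and how effective the particular interventions are". The sample-size paragraph in the same section claims more than 99% "power to detect an 8% absolute reduction in cesarean section rates", assuming a 57% rate across centers and an ICC of 0.3. It gives the odds-ratio equivalent as 0.72.

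The Statistical analysis section specifies a logistic mixed-effects model "with covariates for the trial arm and a categorical term for any underlying trend" and names one measure: "The primary effect measure will be the odds ratio for the arm estimated from this model". The test rule is: "Significance of any difference in the primary outcome is set at 0.05".

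The only rates the article names as outcome quantities are in the Data section: "The outcome variables will be the percentage of primary and secondary outcomes measured during the intervention period". The window also takes in two further months after that. No time adjustment is attached to these percentages.

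**The concern.** The trial asks how many percentage points the cesarean rate moves, and was sized for 8. The named result is on another scale. The planning paragraph seems to connect the two by giving 0.72 beside the 8 points, so a reader will naturally compare the model's odds ratio with 0.72 and conclude that the planned effect was or was not reached.

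That comparison is not like with like. The 0.72 is computed from two average rates, while the model's odds ratio compares observation and intervention within a unit. When units differ a lot, the unit-specific odds ratio lies further from 1 than the marginal one for the same change in the average rate. Reading it as marginal overstates the points gained. The outcome is common (57%), so the odds ratio is not close to a ratio of rates either.

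**Working it through.** **Inputs.** Control rate 57%, target fall 8 points, ICC 0.3, odds ratio 0.72, 20,000–25,000 births (Data section); 22 units, two crossing over per month for 11 months, 8 + 18 months of births (Study design). Assumptions: two-sided 0.05, equal unit sizes for the power check, and normally distributed unit intercepts on the logit scale.

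**1. The plan's odds ratio.** (0.49/0.51) / (0.57/0.43) = 0.9608/1.3256 = 0.725, in line with the stated 0.72. It uses average rates only, so it is marginal. Applied to 57%, 0.72 gives 48.8%, a fall of 8.2 points. The ratio of rates is 0.49/0.57 = 0.86.

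**2. The plan's power.** The Hussey-Hughes variance is I·s²(s² + T·t²) / [(IU − W)s² + (U² + ITU − TW − IV)t²]. Here I = 22, T = 26, U = 286, W = 5,412 and V = 3,938, so the two brackets are 880 and 18,040. With 20,000 births there are 20,000/572 = 34.97 births per unit-month. Using 0.53 × 0.47 = 0.2491 as the within-unit variance, s² = 0.2491/34.97 = 0.00712 and t² = (0.3/0.7) × 0.2491 = 0.1068. The SE is 1.50 points, and power is Φ(8/1.50 − 1.96), above 99.9%. Taking 0.2491 as the total variance instead gives an SE of 1.26 points and higher power. The stated figure of more than 99% reproduces. The effect in this calculation is a difference in proportions.

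**3. Unit-specific odds ratio to points.** Let unit i have logit rate b + u_i, with u_i normal with mean 0 and SD σ. Choose b so that the average of expit(b + u_i) is 0.57. The average rate under intervention is then the mean of expit(b + ln 0.72 + u_i), found by numerical integration.

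- *ICC on the latent logit scale:* σ² = [ICC/(1 − ICC)] × π²/3. At 0.3, σ = 1.187.
- *ICC on the proportion scale:* σ is chosen so that the variance of unit rates is ICC × 0.57 × 0.43. At 0.3 that variance is 0.0735 and σ = 1.541.

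| ICC and scale | Fall at unit-specific OR 0.72 | Unit-specific OR for an 8-point fall |
|---|---|---|
| 0 | 8.2 points | 0.72 |
| 0.1, latent | 7.5 | 0.71 |
| 0.2, latent | 6.9 | 0.68 |
| 0.3, latent | 6.4 | 0.66 |
| 0.3, proportion | 5.7 | 0.63 |

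**4. The same gap in the other direction.** If the true fall is 8 points, the model should give about 0.66 or 0.63. Applied naively to 57%, these give odds of 1.3256 × 0.66 = 0.875 (46.7%) and 1.3256 × 0.63 = 0.835 (45.5%). The apparent falls are 10.3 and 11.5 points instead of 8.

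**5. Why raw percentages cannot fill the gap.** The schedule has 286 observation and 286 intervention unit-months. Their month totals are 2,112 and 5,610, so the mean calendar months are 7.4 and 19.6, about 12 months apart. Any secular change over that year would enter a raw comparison of the two phases.

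**The case against.** The strongest reply is that nothing contradicts anything. A change in rates names the outcome, and the odds ratio is a legitimate scale on which to estimate it. The planned odds ratio is adjusted for time, and the target is given on both scales. An absolute measure derived from the fitted model is the kind of detail that an article leaves to the full protocol or the SAP, neither of which is shown. Recruitment was to end in October 2023, only weeks after this protocol version, and results were visible to the units throughout, so replacing the primary effect measure now could look data-driven.

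Most of this stands. Four stronger readings that a reader might infer are not supported:

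- *That no adjusted rate change will ever be produced.* Naming a primary measure excludes no others, and the planned model can supply a rate difference.
- *That the trial plans a crude comparison of phases.* The Data section lists percentages for the intervention period and the two months after it, and the main analysis is the mixed model.
- *That significance well below 8 points is a defect.* The 8 points are a power input and are nowhere called a success margin. Any design with more than 99% power has this property.
- *That the power or the 0.72 is wrong.* Both reproduce.

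The reply does not dispose of the two-scale argument. The planning value of 0.72 and the model's odds ratio are different quantities, so giving the target on both scales does not make the estimate comparable with it.

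**Conclusion.** The point holds as a cheap improvement, not as an error in the primary test. For an outcome and planning target expressed as an absolute rate change, the article names only a time-adjusted, unit-specific odds ratio. Set against 0.72, that estimate can mislead: at a 57% control rate and ICC 0.3, a unit-specific 0.72 is about 6.4 points (latent scale) or 5.7 points (proportion scale), roughly 80% or 71% of the planned 8.

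The size rests on the ICC scale, which the article does not state, and on normal unit effects. The gap shrinks as the ICC falls: at a latent ICC of 0.1 the same odds ratio is 7.5 points, and with no between-unit variation it disappears.

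**What to change.** In the Statistical analysis section, keep the odds ratio as the primary effect measure and the basis of the test, and add a sentence to this effect: the time-adjusted difference in cesarean rate, in percentage points with a 95% CI, will be reported beside the odds ratio; it is obtained from the primary model by predicting every birth under observation and under intervention in its own unit and month and averaging the two sets of predictions, with the CI by the delta method or a unit-level bootstrap.

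Compare this difference, and not the conditional odds ratio, with the 8-point planning figure. In the sample-size paragraph, label 0.72 as the marginal conversion of 57% to 49%. In the Data section, label the outcome percentages as descriptive.

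The cost is some post-estimation code and one more reported estimate. The model, test, p-value and sample size are unchanged, and no new success rule is needed. Because the odds ratio stays primary, the late date of the change is not a serious obstacle. The addition should still be dated and described as supplementary.

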The online courses and hands-on workshops will be given on consecutive days and will be conducted by experienced trainers. Training groups will be limited to only the participating professionals each time in order to ensure adequate training. The purpose of this activity is to make clear the study’s objectives, which are to focus on the need for evidence-based clinical practice and to review the HSOG Guidelines on labor induction, cesarean section, and vaginal birth after cesarean section, along with HSOG’s consent forms. Another crucial aim is to pinpoint what are the barriers to the use of these guidelines in the participating obstetric departments, overcome these barriers, and eventually implement the guidelines.5.Throughout the intervention period, compliance with guidelines will be enhanced by regular follow-up meetings with the Principal Investigator, members of the committees, and local principal investigators or opinion leaders participating in the study, via either physical presence, teleconferences, or phone calls. Feedback will also be adjusted independently based on locally preferred routes of better tailoring the intervention to the unit’s daily practice. Additional visits may follow if deemed necessary based on platform statistics.6.A member of the study’s staff will visit each unit every 3 months. During the visit, she/he will accommodate data acquisition and local participating obstetricians’ familiarity with the study’s platform while also serving the study committees’ actions indicated locally. A number of at least four visits per participating unit is estimated.7.Use of the Robson 10-group classification criteria embedded in the electronic questionnaire (Table 5) and written feedback on the unit’s cesarean section rates on a regular basis will identify the higher categories that should and may be reduced further.8.Live real-time statistics will be provided, as demanded by the unit basis, to enable the participating units to see their performance. This type of feedback is expected to improve adherence to the interventions.9.Cesarean section and CTG interpretation meetings will be held once to twice monthly during which cesarean sections and “abnormal” CTG cases will be discussed. Participants will be the units that are at the intervention phase of the study precisely when the meeting takes place. The members of steering committee and local contributors to the study may actively participate in these meetings by physical presence, teleconference, or phone call. This is expected to further enhance compliance.10.Reminders about good obstetric practice will be placed in labor wards, staff rooms, and above theater hand wash basins. These will be short printed messages on the importance of improving the rate of vaginal birth offering birth attendants hints to reduce cesarean section rates. The reminder-texts will be planned in accordance with preferred recommendations, carefully considering the defining features and the barriers to the adoption of evidence-based birth practices and to the use of the guidelines in Greece. These reminders will also be sent to the participants by newsletters and mobile sms. Every week they will receive a different reminder. When the existing reminders come to an end, a restatement of the reminders will follow again by newsletter.

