**Robson classification**	
1	Nulliparous, single cephalic, ≥ 37 weeks, in spontaneous labor
2	Nulliparous, single cephalic, ≥ 37 weeks, induced or cesarean section before labor
3	Multiparous (excluding previous cesarean section), single cephalic, ≥ 37 weeks, in spontaneous labor
4	Multiparous (excluding previous cesarean section), single cephalic, ≥ 37 weeks, induced or cesarean section before labor
5	Previous cesarean section, single cephalic, ≥ 37 weeks
6	All nulliparous breeches
7	All multiparous breeches (including previous cesarean section)
8	All multiple pregnancies (including previous cesarean section)
9	All abnormal lies (including previous cesarean section)
10	All single cephalic, < 37 weeks (including previous cesarean section)

This type of study was chosen as the optimal method to examine the effects of a new intervention applied in several population groups and analyzing/measuring the performance of the intervention for each unit’s population individually and as a whole. As already mentioned, the intervention study is characterized by a random sequel from the observation status to the intervention mode in different time intervals (every month) for each two of the participating units. This will create informative data at each step for both the observation and intervention periods.

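### The primary model has no birth-level case-mix terms, and adjustment is an optional sensitivity analysis triggered by seeing imbalance, so a within-unit change in who is enrolled after crossover would pass into the primary odds ratio

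*Protocol article*

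**What the plan says.** The Statistical analysis section specifies a mixed effects logistic regression "with covariates for the trial arm and a categorical term for any underlying trend". It then says: "The primary effect measure will be the odds ratio for the arm estimated from this model". No woman-level covariate is in that model.

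Case mix appears two paragraphs later: "if baseline imbalances are obvious and of clinical relevance between control and intervention periods, the above models may be adjusted for these imbalances", and this is to be done "via a further sensitivity analysis". So adjustment is optional, depends on what the data show, has no named covariates and no criterion, and does not touch the primary estimate.

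Other parts of the article bear on the point:
- **Data section.** The data will be used to examine confounding from imbalances due to group randomization, but no model is fixed. Data collectors will know when they are in the intervention period.
- **Study design, after Table 1.** The enrolled obstetricians obtain the women's consent.
- **Randomization section.** Minimization uses baseline cesarean rate, region and unit size, all at unit level.
- **Interventions, item 7.** Case-mix data are collected: "Use of the Robson 10-group classification criteria embedded in the electronic questionnaire".
- **Table 5.** The groups are defined by parity, previous cesarean, plurality, presentation, gestational age and onset of labor. Group 2, for example, is "Nulliparous, single cephalic, ≥ 37 weeks, induced or cesarean section before labor".

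**The concern.** Previous cesarean and parity are settled before labor, are expected to predict cesarean strongly, and are already asked about. The person who enrolls each woman knows the period and receives feedback on the unit's cesarean rate. If the mix of enrolled women changes when a unit crosses over, the change coincides exactly with the arm indicator, and a model with only unit, time and arm terms attributes it to the intervention. A fall in the share with a previous cesarean would exaggerate the benefit; a rise would hide some of it.

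The trigger adds a second problem. Whether imbalance is large enough to adjust for, and for which variables, would be decided after the data are seen, in a trial whose data and results are described as available at any time. An unspecified adjustment could also use the full Robson group, which contains variables that the intervention is meant to change.

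**Working it through.** **1. The plan's own figure.** Inputs from the article: 57% falling to 49%, ICC 0.3, alpha 0.05, 22 units, two crossing each month for 11 months, 8 + 18 = 26 months of births, 20,000 births. Assumed: a two-sided test, equal unit-months, total variance at the mid-rate of 0.53.

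- OR = (0.49/0.51)/(0.57/0.43) = 0.725 (stated 0.72).
- Births per unit-month: 20,000/(22 × 26) = 34.97. Total variance: 0.53 × 0.47 = 0.2491.
- The Hussey and Hughes formula gives a risk-difference SE of 0.01257. Then 0.08/0.01257 = 6.36, and power = Φ(6.36 − 1.96) = 99.9995%.
- For ICC from 0.01 to 0.5, power is at least 99.97%.

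The stated power above 99% is reproduced and does not depend on case-mix adjustment.

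**2. What the model terms remove.**

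| Source of case-mix difference | Removed by |
|---|---|
| Stable difference between units | unit effect |
| Trend common to all units | time terms |
| Change within a unit at its crossover | nothing in the primary model |

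The optional extensions do not fill the last row. A random effect for time allows units to drift differently. A random unit-by-arm term allows the effect to vary. Neither separates an average enrolment shift at crossover from an average effect.

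**3. Size of the unprotected bias.** The article gives no case-mix rates, so these are assumptions. Let q be the share with a previous cesarean and c their cesarean rate. With 57% overall, the rate in the others is d = (0.57 − qc)/(1 − q). If the share falls by s after crossover and nothing else changes, the rate becomes 0.57 − s(c − d), and the spurious OR is its odds divided by 0.57/0.43.

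Example: q = 0.15, c = 0.90. d = (0.57 − 0.135)/0.85 = 0.512. For s = 0.02 the rate falls by 0.02 × 0.388 = 0.0078 to 0.5622, and OR = (0.5622/0.4378)/1.3256 = 0.969.

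| q | c | d | OR, s = 2 points | OR, s = 3 points | OR, s = 5 points |
|---|---|---|---|---|---|
| 15% | 90% | 0.512 | 0.969 | 0.954 | 0.924 |
| 20% | 90% | 0.487 | 0.967 | 0.951 | 0.920 |
| 25% | 90% | 0.460 | 0.965 | 0.948 | 0.915 |
| 20% | 95% | 0.475 | 0.962 | 0.944 | 0.908 |
| 25% | 95% | 0.443 | 0.960 | 0.940 | 0.902 |
| 30% | 95% | 0.407 | 0.957 | 0.936 | 0.896 |

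In risk terms this runs from 0.8 points (0.02 × 0.388) to 2.7 points (0.05 × 0.543), or about 10% to 34% of the 8-point target.

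One shift was also simulated: 2 points, no true effect, ICC 0.05, 20% previous cesarean, 45% nulliparous, 40 runs. The unadjusted OR averaged 0.96 and the adjusted OR 1.00. With no shift, both averaged 0.99. The 3- and 5-point figures rest on the arithmetic alone.

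**4. What adjustment does to precision.** Previous cesarean alone explains q(1 − q)(c − d)²/(0.57 × 0.43) of the outcome variance, or 8% to 25% over the table. If covariates explain 10–30% of the within-unit variance, the risk-difference SE falls from 0.0126 to 0.0119–0.0105, and the difference detectable with 90% power falls from 4.1 to 3.9–3.4 points.

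The log odds ratio behaves differently. The simulation (20,000 births, equal units, unit and month as fixed effects, conditional OR 0.725, 25 runs per scenario) gave:

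| ICC | SE of log OR, unadjusted → adjusted | OR | mean absolute z |
|---|---|---|---|
| 0.05 | 0.061 → 0.067 | 0.77 → 0.73 | 4.25 → 4.68 |
| 0.3 | 0.066 → 0.073 | 0.77 → 0.73 | 4.03 → 4.38 |

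The SE rises, the OR moves away from 1, and the test statistic gains about 9–10%.

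**5. Why not the full Robson group.** Groups 1 and 2, and groups 3 and 4, differ only by spontaneous labor versus induction or pre-labor cesarean. The intervention includes guidelines on induction and on cesarean section (Table 4) and training in external cephalic version (Table 3). Onset of labor, gestational age at birth and presentation at birth can therefore be changed by the intervention, and conditioning on them could remove part of its effect.

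**The case against.** An unadjusted stepped-wedge model with arm and time terms is a valid analysis and matches the basis of the power calculation. The trigger governs only a sensitivity analysis, so it cannot alter the primary result. The rule asks for clinical relevance as well as visibility, the Data section promises a look at confounding, and a covariate list is commonly left to an analysis plan that is not shown. All of that stands. It does not answer the point, because the article does not leave adjustment open: it places it outside the primary model and makes it depend on what is seen.

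Three stronger readings are tempting and are not supported:
- **That the primary odds ratio loses precision.** A reader might infer that adjustment would narrow its interval. On the log-odds scale the SE rises. The gain is in the test statistic and the risk difference, and power is already above 99%.
- **That case-mix drift is likely.** Nothing in the documents shows that enrolment will change at crossover. Unequal unit size and pairwise crossover do not cause drift. The documents show only that unblinded enrolment makes it possible.
- **That the primary analysis is invalid.** It is biased only if such a shift occurs.

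Two limits also stand. Adjustment does not correct selection on unmeasured factors. And this protocol version is dated about six weeks before recruitment was due to end, so a change to the primary model is a late one.

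**Conclusion.** The point holds as a weakness in protection and prespecification. A within-unit shift in the previous-cesarean share of 2 to 5 points would move the primary odds ratio from 1 to about 0.97–0.90 with no true effect, against a planned 0.72, and the smaller shifts might not meet a visual trigger. This assumes a 15–30% previous-cesarean share, 90–95% cesarean among those women, 57% overall, the same shift in every unit and no other change. The simulation behind the efficiency figures is small and uses equal unit sizes and one case mix. The power statement is not in question. The change should be made because the covariates are already collected, not because the planned analysis fails without it.

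**What to change.** - Put parity, previous cesarean and plurality in the primary model as fixed, prespecified covariates. Keep the unadjusted model as a sensitivity analysis.
- Take them from the underlying questionnaire items, not the group number, because Robson groups 7 to 10 pool women with and without a previous cesarean. This assumes that the items are stored separately.
- Delete the imbalance trigger.
- State that onset of labor, gestational age at birth and presentation at birth, and hence the full Robson group, are not adjusted for because the intervention can change them.
- State that the odds ratio is conditional on these covariates as well as on unit, and report a standardized absolute risk difference beside it.

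The cost is analysis wording and an odds ratio with a more conditional meaning and a somewhat larger SE on the log scale. Because the trial is near its end and units see live statistics, the change should be dated, recorded before the comparative analysis, and reported as late. If it is judged too late for the primary model, a mandatory adjusted analysis with the same covariate list, reported beside the primary result, keeps most of the benefit.
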